## Abstract

**Background:**

Developed countries are facing a huge rise in the prevalence of obesity and its associated chronic medical problems. In the UK Primary Care Trusts are charged with addressing this in the populations they serve, but evidence about the most effective ways of delivering services is not available. The aim of this study is to determine the effectiveness of a range of weight loss programmes for obese patients in primary care and to determine the characteristics of patients who respond to an invitation to a free weight management programme.

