This research protocol was developed in response to a need for South Birmingham Primary Care Trust (PCT) to develop services for the management of obesity. The PCT had identified that there were insufficient weight management services available in the National Health Service (NHS) and wished to develop these. As part of this, general practitioners (GPs) had been contracted to record height and weight of their patients. One option was for GP practices or NHS pharmacies to provide weight management services, for which the PCT would reimburse these practitioners. However, in the UK, there are many well established commercial companies that provide weight management services that are widely recognised and commonly used by those seeking help to lose weight. The PCT wished to contract with services that would have a high reach, good acceptability, and showed evidence of effectiveness and cost-effectiveness. Thus the aim of this trial was to determine the effectiveness of a range of NHS and commercial weight loss programmes in an unselected primary care population and to determine the characteristics of people responding to an unsolicited letter of invitation from their general practitioner.

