### Population

Eligible participants are registered with general practices in South Birmingham Primary Care Trust, aged ≥ 18 years, with a raised BMI recorded within their primary care notes within the previous 15 months. The BMI threshold for invitation is that which makes them eligible for primary care obesity management services within the NHS and varies according to ethnic group and the presence or absence of co-morbidities. The threshold for invitation for people with no obesity-related comorbidity is a BMI of ≥ 30 Kg/m^2 ^in any ethnic group except South Asian and BMI ≥25 Kg/m^2 ^in South Asians. For people with obesity related comorbidity the threshold for invitation is a BMI ≥ 28 Kg/m^2 ^for all ethnicities apart from South Asians, for whom it is BMI ≥ 23 Kg/m^2^.

Their GP has to confirm that they have no medical contra-indications for any of the intervention programmes. Patients are excluded if they are unable to understand English, are pregnant or are unwilling to be randomised.

Recruitment commenced in January 2009. Each general practice identifies eligible patients using a search of the computerised clinical record and invites them by standard letter to participate in the weight loss trial. Practices are asked to exclude patients with serious co-morbidities for whom weight loss programmes were unfeasible or inappropriate, for example those with terminal illness. The invitation letter contains information about the trial and a toll-free telephone number for a call centre managing the recruitment and randomisation. The nurses at the call centre provide more information to patients about the trial, answer questions, collect baseline information, take verbal consent and randomise patients to the trial arms. The call centre books participants into their first treatment session and sends confirmation, along with verification of consent and information on how to withdraw from the trial if they change their minds. Participants allocated to the general practice, pharmacy or minimal exercise intervention (comparator) arms are sent details about how to arrange their first session.

The randomisation sequence was prepared by an independent statistician and to ensure blinding, each allocation was placed in an opaque, consecutively numbered envelope. These are used in order by the call centre staff, who record the number of the envelope and time of randomisation to enable the study team to check these are used in the correct order.

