### Planned analysis

Both between and within group analyses for primary and secondary outcomes at programme end and 12 months will be performed according to intention to treat. Participants in whom weight at follow up is not available will be assumed to have their baseline weight. However, sensitivity analysis will also be undertaken, assuming follow up weight to be the last recorded weight.

As the outcomes are all measured on a continuous scale (weight loss, percentage weight loss, self-reported physical activity), differences between intervention group and the comparison (minimal intervention) group will be investigated using least squares linear regression. Between group analyses will be expressed as both unadjusted and adjusted differences (corrected for baseline score and covariates of age, gender, ethnicity and educational level). A secondary analysis will compare the outcomes of the commercial weight loss programmes (Weight Watchers, Slimming World and Rosemary Conley) with the primary care programmes (general practice and pharmacy-based interventions). Data on choice of programme, number of sessions attended and reasons for drop-out will be presented using descriptive statistics.

To determine whether the service reaches those most in need, the age, gender, and deprivation score (derived from the postcode of residence) of those who were randomised will be compared to those who received the letter but did not respond or declined to be randomised.

Responses to open-ended questions about experience of the service and reasons for dropping out of their allocated programme will be categorised and presented descriptively.

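### The second aim is to describe who responds to the GP's letter, but the planned analysis compares only the randomised with everyone else and never contrasts responders with non-responders

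*Protocol article*

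**What the plan says.** The Abstract gives the second aim as "to determine the characteristics of patients who respond to an invitation to a free weight management programme". The Background repeats it: "to determine the characteristics of people responding to an unsolicited letter of invitation from their general practitioner". The Discussion adds that the study can examine how far obesity services are taken up once people are invited.

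The Population section sets out the order of events: "The invitation letter contains information about the trial and a toll-free telephone number for a call centre managing the recruitment and randomisation". Nurses at the call centre then give further information, collect baseline data, take verbal consent and randomise. The same section says: "Patients are excluded if they are unable to understand English, are pregnant or are unwilling to be randomised".

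Planned analysis introduces the relevant comparison with the purpose "To determine whether the service reaches those most in need". It names three variables (age, gender and a deprivation score based on postcode) and then fixes the groups: "those who were randomised will be compared to those who received the letter but did not respond or declined to be randomised".

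**The concern.** The aim concerns response to a letter. The analysis concerns entry to a randomised trial. These are separate steps, and some people take the first without the second. A caller who will not accept allocation by chance has responded, but the planned comparison puts that person on the side of those who did not.

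The second aim, stated twice, therefore has no analysis that answers it directly. A table of the randomised against the rest may be read as a profile of responders when it is a profile of trial entrants. The Background says that the Primary Care Trust wanted services with high reach, so this is a result that the commissioner would use. This is a stated rule that does not match a stated aim, rather than detail that an article leaves to a fuller document.

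**Working it through.** **Setting the sections side by side**

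1. Aim (Abstract, Background): the group of interest is everyone who responds to the letter.
2. Route (Population): responding means telephoning the call centre; consent and randomisation come later.
3. Consequence: responders comprise the randomised, those who decline randomisation, and those excluded after contact for another reason such as pregnancy.
4. Planned analysis: the index group is the randomised only. Decliners are on the comparison side. Responders excluded for other reasons belong to neither group as worded.
5. No other sentence in Planned analysis compares responders with non-responders.

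**How much could it matter?**

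The article gives no figure for the reach analysis, so there is none to reproduce. The one documented input is the number randomised (Sample size): 6 × 100 + 2 × 70 = 740. Everything else below is assumed: N = 5,000 invited; D decliners; a 'most deprived' share of 30% in the randomised (pR) and 40% in non-responders (pN); and a share pD in decliners that is varied. Other exclusions are ignored.

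- Planned contrast, comparison side pooled = pR − [D·pD + (N − 740 − D)·pN] / (N − 740)
- Responder contrast = (740·pR + D·pD) / (740 + D) − pN

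Example with D = 370 and pD = 50%:

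- Planned: 0.30 − (185 + 1,556)/4,260 = 0.30 − 0.409 = −10.9 points
- Responder: (222 + 185)/1,110 − 0.40 = 0.367 − 0.40 = −3.3 points

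Each cell gives planned / responder contrast in percentage points:

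| Decliners (share of responders) | pD = 50% | pD = 40% | pD = 30% |
|---|---|---|---|
| 40 (5.1%) | −10.1 / −9.0 | −10.0 / −9.5 | −9.9 / −10.0 |
| 150 (16.9%) | −10.4 / −6.6 | −10.0 / −8.3 | −9.6 / −10.0 |
| 370 (33.3%) | −10.9 / −3.3 | −10.0 / −6.7 | −9.1 / −10.0 |
| 740 (50.0%) | −11.7 / 0.0 | −10.0 / −5.0 | −8.3 / −10.0 |

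With 8,000 invited the responder contrasts are unchanged and the planned contrasts move by at most 0.7 points.

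If the comparison side were split into two groups, randomised versus non-responders would be 30% − 40% = −10.0 points in every cell. The mismatch with the responder contrast would remain wherever decliners differ from the randomised.

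**The case against.** Several points on the other side are fair.

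- *The word 'or' may name two comparison groups, tabulated separately in a fuller document.* That is possible. The index group would still be the randomised, so the responder contrast would still be absent.
- *Planned analysis states its own purpose, reach of the service, and only randomised people enter a programme.* Randomised versus not randomised is a defensible description of programme uptake and should stay. It does not answer the aim in the Abstract and Background.
- *Callers are themselves selected by a letter about a trial.* This stands. People put off by randomisation may never telephone, so the responder contrast would not equal the reach of a commissioned service either. That limits interpretation, but it is no reason to put known callers with people who did not reply.
- *Decliners may not want the service.* Also fair: the article plans no record of why callers decline randomisation. A reader might infer that decliners are people who wanted help and were lost only to randomisation. The text does not show this, and the point does not need it.

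A reader might also infer that need cannot be judged because body mass index and comorbidity are not compared. The article does not support that. Deprivation is a legitimate indicator of need, every invitee already meets an NHS eligibility threshold, and those thresholds differ by ethnicity and comorbidity, so raw body mass index would be hard to compare. Adding such fields, or adjustment for practice, is a preference. The former would also mean new data extraction for people who have not consented.

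**Conclusion.** The point holds as a mismatch between a stated aim and a stated analysis. The article sets out to describe responders but plans only a comparison of the randomised with those not randomised, with decliners among the latter. This rests on reading 'respond' as making contact with the call centre, which is the only route that the Population section describes.

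The size is undetermined. In the illustration the two contrasts differ by about 1 point or less with 40 decliners. They differ by at most 1.7 points if decliners resemble the randomised, even when half of responders decline. Gaps of several points need many decliners who also differ from the randomised, such as −10.9 against −3.3 points with 370 decliners at 50%. Nothing in the article says which case applies. A reader might conclude that the reach result is materially biased; the documents do not show that, and the figure for the randomised would be correct for the group that it describes.

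The aim is descriptive and secondary, and the treatment comparisons are untouched. The change is still worth making, because without it the second aim has no direct answer.

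**What to change.** Amend Planned analysis as follows.

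1. Define a responder as an invitee who contacted the call centre after the letter.
2. Report age, gender and deprivation score for three groups: non-responders, responders not randomised for any reason, and the randomised.
3. For the stated aim, compare all responders (the second and third groups together) with non-responders.
4. Keep randomised versus not randomised as a separate comparison, labelled as trial or programme uptake.
5. State that responders answered a letter describing a trial, so the result is not the reach of a commissioned service.

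The cost is small. The variables and most of the categories are already named, and the existing comparison is kept. Call-centre contacts who are not randomised must be identifiable as a category of their own. The article does not say whether they are logged, and recruitment began in January 2009, so this should be checked for contacts already made.

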### Costs

An NHS perspective will be taken in the cost analysis. The price to the PCT of each programme will be used. The cost of the call center which co-ordinated the service will be calculated as an average per person, based on the numbers of staff employed over a 12 month period and clients who used the service over this time period. The mean cost per kg of weight lost will be determined for each programme.

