The participants allocated to the commercial operators Weight Watchers [20], Slimming World [21] and Rosemary Conley [22] have a choice of programme locations and times. Commercially, these programmes run continuously, with no set number of sessions and no fixed starting date. People who are not participating in the trial pay fees to attend these programmes and these people attend alongside those in the trial, for whom treatment is free. Each programme is provided in accordance with the respective organisations' guidance and the group leaders are trained by the organisations. The vouchers provided to trial participants exempts them from payments for the first 12 weeks of the programme. Thereafter, if participants wish to continue attending sessions they are required to pay the appropriate fees to the service provider. The Size Down Programme is an NHS group-based programme in which all members of the group commence together and follow a prescribed course of sessions. It takes place in various community venues. Participants randomised to the general practice or pharmacy arms attend one-to-one sessions in the general practice or pharmacy. Appointments are made at a time mutually convenient to the participant and the nurse/pharmacist.

In the choice arm, participants are able to choose from any of the intervention programmes described above.

Participants allocated to the comparator group are sent vouchers for 12 free sessions to attend a local authority run leisure centre (typically including an exercise room, swimming pool, and other facilities such as squash or badminton courts). Participants are not given an appointment to attend and are given no dietary or individual physical activity advice and support. It is acknowledged that weight loss can occur with exercise-only, but effects are modest [8,23].

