## Discussion

A quarter of the UK population and a similar high proportion in other countries are obese. If primary care clinicians were to manage this disorder, it would potentially mean a large proportion of their time being devoted to it. Commercial weight loss organizations have a large network of treatment services that provide a cheaper alternative to primary care services. However, the comparative effectiveness and the cost-effectiveness is unknown. This trial aims to provide these data.

One important aspect to this work is that it is a weight loss trial recruiting in primary care among those who have not specifically sought treatment. Many published weight loss intervention trials treat patients in specialist obesity clinics. These clinics provide treatment for only a minority of all people who need it. In particular, in this study, we will be able to examine uptake of obesity management services in response to an invitation. We are not aware of any other study that has examined uptake in a defined population in this way.

Robust clinical trial results are not available for all the commercial providers in this trial and for few primary care led programmes, so this research will extend knowledge about the efficacy of commercial and community weight loss programmes. In addition our participants were responders to an invitation from their general practitioner, whereas many other trials have recruited volunteers, who are likely to be more motivated to lose weight. This trial will inform decisions about which weight loss programmes might make useful clinical contributions for patients with obesity and which might have useful contributions to reducing the public health toll of obesity.

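### The planned cost per kg lost is an average within each programme that leaves out the comparator, so it does not deliver the comparative cost-effectiveness the protocol says the trial will provide

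*Protocol article*

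**What the plan says.** The Costs section of the protocol article sets the perspective ("An NHS perspective will be taken in the cost analysis") and two cost inputs. For the programmes, "The price to the PCT of each programme will be used". For the shared service, "The cost of the call center which co-ordinated the service will be calculated as an average per person". It then names the single economic result: "The mean cost per kg of weight lost will be determined for each programme". The section mentions no comparator cost, no comparator weight loss and no difference in either.

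Three other places bear on this:

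- **Discussion**, on cheaper commercial alternatives to primary care: "However, the comparative effectiveness and the cost-effectiveness is unknown. This trial aims to provide these data". The Background adds that the commissioner wanted to contract with services that "showed evidence of effectiveness and cost-effectiveness".
- **Planned analysis**: effectiveness is estimated as a difference between each intervention group and the minimal-intervention group by linear regression, unadjusted and adjusted.
- **Interventions**: the comparator is not an empty arm. "Participants allocated to the comparator group are sent vouchers for 12 free sessions to attend a local authority run leisure centre", and "It is acknowledged that weight loss can occur with exercise-only, but effects are modest".

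**The concern.** Cost divided by weight lost in the same arm credits a programme with all the weight its participants lose, including what they would have lost with leisure-centre vouchers alone. The protocol itself expects some loss of that kind. The effectiveness analysis removes it by comparing with the randomised control group, but the cost measure as worded does not.

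A commissioner choosing between services needs to know what each extra kilogram costs over the minimal alternative, and what a dearer programme buys over a cheaper one. An average ratio answers neither question. It can make a programme look inexpensive per kilogram when most of its loss would also have occurred in the comparator arm. A programme no better than the vouchers would still show a finite and possibly attractive figure.

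**Working it through.** **Inputs.** From the Sample size section: a 2 kg design difference against the comparator, standard deviation 3.2 kg, 90% power, 5% significance and 20% dropout. The documents give no programme price, voucher price, call-centre cost or expected comparator loss. All such values below are assumptions in arbitrary money units.

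**1. The plan's own figure.** No cost figure is stated. The sample size that supplies the 2 kg reproduces. With two-sided 5%, n = 2 × (3.2 × (1.960 + 1.282) / 2)² = 53.8, so 54 per arm, and 54 / 0.8 = 67.5, so 68. A t-based calculation needs 55, and 55 / 0.8 gives 69. The protocol states 70. The total is 6 × 100 + 2 × 70 = 740. None of this is in dispute.

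**2. The two measures.** Let K and W be a programme's mean cost and mean loss, and Kc and c the comparator's.

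- Average ratio (the plan): K / W
- Incremental ratio: (K − Kc) / (W − c)

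Cross-multiplying, the average is below the incremental ratio when Kc × W < K × c. They agree when Kc and c are both zero, and otherwise only by coincidence. A call-centre cost that is the same per person in every arm cancels from K − Kc but stays in K / W.

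**3. Size at the design difference.** Put W = c + 2 and Kc = 0. The average is K / (c + 2) and the incremental ratio K / 2, so the average understates by the factor (c + 2) / 2. With K = 100:

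| Comparator loss c (kg) | Average | Incremental | Factor |
|---|---|---|---|
| 0 | 50.0 | 50.0 | 1.00 |
| 0.5 | 40.0 | 50.0 | 1.25 |
| 1 | 33.3 | 50.0 | 1.50 |
| 2 | 25.0 | 50.0 | 2.00 |

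**4. Can the order change?** Assume programme A costs 50 and loses 2.5 kg, and programme B costs 90 and loses 4.0 kg. The average ratios are 50 / 2.5 = 20.0 and 90 / 4.0 = 22.5, so A ranks first. The incremental ratios are:

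| c (kg) | Kc | A | B | First |
|---|---|---|---|---|
| 0.5 | 0 | 50/2.0 = 25.0 | 90/3.5 = 25.7 | A |
| 1 | 0 | 50/1.5 = 33.3 | 90/3.0 = 30.0 | B |
| 2 | 0 | 50/0.5 = 100.0 | 90/2.0 = 45.0 | B |
| 1 | 20 | 30/1.5 = 20.0 | 70/3.0 = 23.3 | A |
| 1.5 | 20 | 30/1.0 = 30.0 | 70/2.5 = 28.0 | B |
| 2 | 20 | 30/0.5 = 60.0 | 70/2.0 = 35.0 | B |

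The order reverses in some rows and not in others.

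**5. Distortion without reversal.** With a comparator costing 20 and losing 2 kg, a programme costing 100 and losing 3 kg has average 100 / 3 = 33.3 and incremental 80 / 1 = 80.0. One costing 60 and losing 4 kg has 60 / 4 = 15.0 and 40 / 2 = 20.0. Both figures move, but the second programme is first either way.

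**6. Programme against programme.** B against A costs (90 − 50) / (4.0 − 2.5) = 26.7 per extra kg, whatever the comparator does. Neither average ratio shows this number.

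**The case against.** The case on the other side has real weight.

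- **This is a short cost paragraph, and cost is not a listed outcome.** The primary and secondary outcomes are weight and physical activity, and the aim sentence closing the Background names effectiveness and responder characteristics. This stands, and it limits the importance of the point. But the Discussion does promise cost-effectiveness data, and the Costs section names a specific measure that does not supply them. That is a chosen measure, not a detail left to a fuller document.
- **The text does not say the comparator is excluded.** True. That is read from a figure given for each programme, with no incremental term anywhere in the section.
- **Every magnitude is assumed.** Also true. The protocol calls exercise-only effects modest, and a 2 kg comparator loss equals the whole design difference. The distortion shrinks as comparator loss and cost approach zero.

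A reader might also infer stronger claims that the documents do not support:

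- **That programmes will be ranked wrongly.** Reversal depends on costs and losses nobody has stated, and several assumed settings leave the order unchanged.
- **That the measure is undefined because some individuals lose nothing**, for instance those with missing follow-up set to baseline weight. One price per programme and an averaged call-centre cost point to a ratio of means, which individual zeros do not make undefined.
- **That intervals or acceptability curves are wrongly missing.** An article may leave these to the full plan.
- **That the randomised contrast is abandoned.** It remains the effectiveness analysis and is missing only from the cost measure.

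**Conclusion.** The point holds in a limited form. As written, the only economic result is an average cost per kg within each programme, and it does not provide the comparative cost-effectiveness claimed in the Discussion. At the 2 kg design difference with zero comparator cost, it understates the cost per extra kg by a factor of 1.25 to 2.0 for an assumed comparator loss of 0.5 to 2 kg. With a positive comparator cost the gap narrows and can vanish: programme A at c = 1 kg and Kc = 20 gives 20.0 on both measures. A change in programme order is possible but not certain. The primary outcome and its analysis are unaffected.

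**What to change.** In the Costs section, make the main economic result the incremental cost per additional kg lost against the comparator: the difference in mean cost divided by the between-group difference in weight loss already planned. Assign the leisure-centre voucher cost to the comparator arm and the call-centre cost to every arm. Because ratios against one common comparator do not by themselves settle a choice among several programmes, set aside dominated programmes and compare the remaining ones with each other incrementally. Keep the average cost per kg, stated to be a ratio of means, as description only.

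The cost is small: revised wording and a little more analysis, with no new patient data. One input must be added. The protocol gives neither the voucher price nor who bears it, and under an NHS perspective both matter, since the leisure centres are run by the local authority.
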